## PROTOCOL SUMMARY

### QUESTION ADDRESSED

What is the clinical and cost-effectiveness of the use of extracorporeal shockwave lithotripsy (ESWL), compared to ureteroscopic treatment, as the first treatment option for symptomatic ureteric stones that require an active intervention?

### CONSIDERED FOR ENTRY

Male and female patients aged  $\geq 16$  years with a ureteric stone confirmed by non-contrast computed tomography of the kidney, ureter and bladder (CTKUB).

### POPULATIONS

Adults presenting with a ureteric stone within any segment of the ureter, confirmed by CTKUB, able to undergo either ESWL or ureteroscopy, where both the patient and clinician judge intervention to be necessary.

### STUDY ENTRY

Consent to the RCT will be obtained from 750 eligible patients after written and oral information is provided by local hospital teams. Eligible and consenting participants will be randomised to one of the two intervention groups. Randomisation will be stratified by centre, stone size ( $\leq 10$ mm or  $> 10$ mm, as measured by the maximum stone diameter on CTKUB) and location of the stone in either the upper, mid or lower ureter (as defined in the European Association of Urology-American Urological Association (EAU-AUA) Guidelines). Participants will be followed-up by postal questionnaires sent from the trial office (CHaRT, Aberdeen) at eight weeks and six months after randomisation and from their health record.

### INTERVENTIONS

- Extracorporeal shockwave lithotripsy (ESWL)
- Ureteroscopic treatment

### OUTCOME ASSESSMENT

The primary clinical outcome is clinical resolution of the stone episode (defined as no further intervention required to facilitate stone clearance) up to six months from randomisation.

The primary economic outcome is the incremental cost per quality adjusted life years (QALYs) gained at 6 months from randomisation. QALYs are based on the responses to the EQ-5D.

### CO-ORDINATION

**Local:** by the local consultant Urologists, urology team and research nurses

**Central:** by Study Office in Aberdeen ([contact])

**Overall:** by the Project Management Group, and overseen by the Steering Committee and the Data Monitoring Committee

### FUNDER

The National Institute for Health Research (NIHR), Health Technology Assessment (HTA) Programme. Number 10/137/01

**Funding start date:**  
**Funding end date:**

1 March 2013  
28 February 2017

| GLOSSARY OF ABBREVIATIONS |                                                                 |
|----------------------------------|-----------------------------------------------------------------|
| AE                               | Adverse Event                                                   |
| BAUS                             | British Association of Urological Surgeons                      |
| CEAC                             | Cost-effectiveness Acceptability Curve                          |
| CHaRT                            | Centre for Healthcare Randomised Trials                         |
| CI                               | Chief Investigator / Confidence Interval                        |
| CRF                              | Case Report Form                                                |
| CONSORT                          | Consolidated Standards of Reporting Trials                      |
| CTU                              | Clinical Trial Unit                                             |
| CTKUB                            | Computed Tomography Scan of the Kidneys, Ureters and Bladder    |
| DCE                              | Discrete Choice Experiment                                      |
| DMC                              | Data Monitoring Committee                                       |
| EAU-AUA                          | European Association of Urology-American Urological Association |
| eGFR                             | Estimated Glomerular Filtration Rate                            |
| ESWL                             | Extracorporeal Shockwave Lithotripsy                            |
| EQ-5D                            | EuroQol Group's 5 dimension health status questionnaire         |
| GCP                              | Good Clinical Practice                                          |
| GP                               | General Practitioner                                            |
| HRQoL                            | Health Related Quality of Life                                  |
| HSRU                             | Health Services Research Unit                                   |
| HTA                              | Health Technology Assessment                                    |
| ISD                              | Information Statistics Division                                 |
| ISF                              | Investigator Site File                                          |
| ISRCTN                           | International Standard Randomised Controlled Trial Number       |
| IVR                              | Interactive Voice Response (randomisation)                      |
| NHS                              | National Health Service                                         |
| NHSG                             | National Health Service Grampian                                |
| NIHR                             | National Institute Health Research                              |
| NRES                             | National Research Ethics Service                                |
| NRS                              | Numeric Rating Scale                                            |
| PI                               | Principal Investigator                                          |
| PIL                              | Patient Information Leaflet                                     |
| PMG                              | Project Management Group                                        |
| PQ                               | Participant Questionnaire                                       |
| QALY                             | Quality-Adjusted Life Year                                      |
| RCT                              | Randomised Controlled Trial                                     |
| R&D                              | Research and Development                                        |
| REC                              | Research Ethics Committee                                       |
| SAE                              | Serious Adverse Event                                           |
| SAP                              | Statistical Analysis Plan                                       |
| SD                               | Standard Deviation                                              |
| TMF                              | Trial Master File                                               |
| TSC                              | Trial Steering Committee                                        |
| VDS                              | Verbal Descriptor Scale                                         |
| UK                               | United Kingdom                                                  |
| UKCRC                            | United Kingdom Clinical Research Collaboration                  |
| UoA                              | University of Aberdeen                                          |

## 1. INTRODUCTION

### 1.1. Background

Urinary stone disease is very common with an estimated prevalence among the general population of 2–3% (1.8 million people in the UK) with males forming stones three times as often as females. Urinary stones often recur and the lifetime recurrence rate is approximately 50%. The interval between recurrences is variable, with approximately 10% within one year, 35% within five years, and 50% within 10 years. The increased incidence of urinary stones in the industrialised world is associated with improved standards of living (mainly due to the high dietary intake of proteins and minerals) and there is also an association with ethnicity and region of residence. Urinary tract stones, and ureteric stones, in particular, are associated with severe pain as they pass through the urinary tract and can have a significant impact on patients' quality of life due to the detrimental effect on their ability to work and the need for hospitalisation.

Urinary stones are a major burden on the NHS resulting in over 84,323 finished consultant episodes and over 97,558 bed-days in England in 2011 - 2012. When urinary stones move from the kidney into the ureter (tube connecting the kidney to the bladder), they cause severe debilitating pain (ureteric colic) that causes a large transient impairment of quality of life and leads to substantial calls on health service resources. Ureteric colic is the most common cause of emergency admission to Urology departments in the UK and since it predominantly affects younger people (16-55 years) is a common cause of time off work. The aim of treatment for ureteric stones is the immediate relief of symptoms, decompression of the urinary tract and the achievement of clinically complete stone clearance.

Most ureteric stones can be expected to pass spontaneously with supportive care (painkillers and fluids) possibly aided by drugs such as alpha blockers or calcium channel blockers (conservative management). The clinical effectiveness and cost effectiveness of such drug therapy in facilitating stone clearance remains unclear and is the subject of an ongoing HTA commissioned randomised controlled trial led by this research group (due to report in 2014). However, between a fifth and a third of cases require an active intervention (stone removal) because of failure to pass the stone, continuing pain, infection or obstruction to urine drainage. The two standard active intervention options are extracorporeal shockwave lithotripsy (ESWL) and ureteroscopic stone retrieval. Whilst both ESWL and ureteroscopy appear to be effective in terms of stone clearance they differ in terms of invasiveness, anaesthetic requirement, treatment setting, the number of procedures required to clear the stone, complications, patient reported outcomes (such as severity and duration of pain after intervention, time off work and bothersome urinary symptoms), and cost. There is uncertainty around which is the most clinically effective in terms of stone clearance and the true cost to the NHS and to society (in terms of impact on patient reported health and economic burden).

A joint clinical guideline on the management of ureteric stones by the European Association of Urology and the American Urological Association estimates that 68% of stones ≤5 mm and 47% of stones 5-10mm in size can be expected to pass spontaneously and concluded that the majority of these stones pass within four to six weeks of presentation. Stones in the distal ureter pass more readily than stones located more proximally. Consequently, patients with favourable features and with smaller sized stones in the lower ureter are initially treated conservatively. Immediate active intervention occurs in those patients with larger stones and unfavourable features who are deemed clinically to be unsuitable for conservative treatment. Those who fail standard conservative care or who subsequently develop complications also undergo later active treatment. This can be extracorporeal shock wave lithotripsy (ESWL), preliminary ureteric stenting with later stone removal, ureteroscopy with stone retrieval or destruction (in situ lithotripsy), or percutaneous nephrostomy insertion and later stone removal. ESWL and ureteroscopic treatment require expensive equipment and urological expertise. Both have been shown to be options that are safe and effective in a number of studies. In clinical practice urologists tend to favour ureteroscopy over ESWL particularly for mid and lower ureteric stones due to perceived higher rate of clinical stone clearance.

## 1.2. Rationale for the study

A Cochrane systematic review (2007) comparing the effectiveness of ESWL with ureteroscopic management of ureteric stones identified five RCTs involving a total of 732 participants. The results of this review suggest stone-free rates were lower in the ESWL group (RR 0.83 95% CI 0.70 to 0.98) and reflecting this retreatment rates for ESWL were higher (RR 2.78 95% CI 0.53 to 14.71) but these findings are associated with much uncertainty. Complications were less frequent after ESWL (RR 0.44 95% CI 0.21 to 0.92) and this option was associated with a shorter hospital stay (mean difference -2.10 days 95% CI -2.55 to -1.64 days). The review concluded that ureteroscopic treatment of stones was associated with a higher stone free rate but a higher morbidity (complication rate) and a longer hospital stay. However, the overall quality of the studies was poor and inclusion criteria were strict in each study, limiting both the generalisability and applicability of the review findings. There was limited evidence on which to judge the comparative effectiveness in clinically important prognostic subgroups for example location of stones in the ureter. None of the studies reported on health related quality of life and only one reported a cost effectiveness outcome. The review authors recommended that a large scale multicentre RCT was needed to adequately address the effectiveness and cost effectiveness of ureteroscopy versus ESWL. A 2011 update of the Cochrane review has included two further studies but these have not altered the previous conclusions.

The European Association of Urology and the American Urological Association (EAU-AUA) Clinical Guideline Panel on the management of ureteric stones also conducted a review and meta-analysis reporting clinical outcomes and complications following treatment of ureteric stones with ESWL or ureteroscopy, including data from non-randomised comparisons and case series. Pre-defined outcome measures were stone-free rate and number of additional procedures required. The results were stratified according to stone location in the ureter (proximal, mid, distal) and stone diameter ( $\leq 10\text{mm}$ ,  $>10\text{mm}$ ). All forms of ESWL were analysed as a single treatment modality in the meta-analysis. The Panel concluded that the main advantage of ureteroscopy is a higher stone-free rate with a single procedure, but with a higher complication rate. However, the evidence was insufficient for the Panel to recommend between ESWL and ureteroscopy and concluded that for patients requiring active stone removal, either treatment modality is acceptable as first-line options. For the individual patient, the choice is often determined by a number of factors including the availability of resources, preference of the treating urologist, and preference of the patient. The review highlighted design and reporting deficiencies from available studies, including poor definition of stone size, inconsistent reporting of outcomes and lack of randomisation. One of the main recommendations of the Panel was the need to conduct randomised controlled trials (RCTs) comparing the clinical and cost effectiveness of ESWL and ureteroscopy.

In response to the research questions raised by these evidence summaries, the TISU trial will provide the high quality evidence, from a large pragmatic RCT, on the relative effectiveness, and cost effectiveness of ESWL and ureteroscopy, that will inform patients, clinicians and policy makers on the optimal choice of intervention for ureteric stones.

## 2. STUDY OBJECTIVES

The research question that we will address is whether in adults with ureteric stones judged to require active intervention, extracorporeal shockwave lithotripsy (ESWL) is more effective and cost-effective compared to ureteroscopic treatment as the initial management option.

The hypothesis being tested is that outcome in patients receiving ESWL as their first treatment option is not inferior to outcome in patients receiving direct ureteroscopic retrieval.

The clinical and cost-effectiveness of ESWL, as the first treatment option compared with direct progression to ureteroscopic treatment will be determined with respect to the primary outcomes of:

- i. Clinical stone clearance, defined as no further intervention required to facilitate stone passage
- ii. incremental cost per quality adjusted life years (QALYs) and
- iii. disease or treatment-related harms up to 6 months after randomisation.

These outcomes will be measured by:

- The clinical effectiveness of ESWL compared with ureteroscopic treatment in terms of proportion of patients who do not require any further intervention at 6 months
- The cost-effectiveness of a treatment strategy that starts with ESWL compared with one that starts with ureteroscopic treatment at 6 months

A non-inferiority design has been chosen as ESWL offers a less invasive approach, avoiding general anaesthetic, which might avoid the extra cost and more invasive nature of ureteroscopic treatment. If ESWL fails then patients can proceed to ureteroscopy. Our patient group and urologists, who are members of the BAUS Section of Endourology, when asked stated they would prefer the less invasive treatment option and would accept a higher failure rate (up to 20%) and the higher risk of reintervention.

The definitive clinical measure of the effectiveness of ESWL and ureteroscopic treatment for the management of urinary stones is whether the patient's stone is cleared and any symptoms resolved. Current evidence and estimates of the effectiveness of the interventions for management of urinary stones are based upon "stone clearance" as an outcome. However, to assess stone clearance with certainty would require that all patients have repeated computed tomography scans of the kidneys, ureters, and bladder (CTKUB) until the stone is no longer imaged. This is not standard practice because it results in radiation exposure and is unlikely to change patient management. For our primary outcome we have defined stone clearance as no further intervention required to facilitate stone clearance up to 6 months after randomisation. The decision on the necessity of a further intervention (primary outcome) is that of the treating clinician unblinded to the treatment received and so is potentially open to bias based upon the treating clinician's knowledge and perceptions of the efficacy of the intervention. To minimise this possibility the decision that further intervention is required will be based on EAU-AUA guidelines.

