### 4.1 Definitions

An adverse event (AE) is defined as any untoward medical occurrence in a participant, not necessarily having a causal relationship.

Adverse events are not:

- continuous and persistent disease or symptom, present before the trial, which fails to progress;
- signs or symptoms of the disease being studied (in this case ureteric stones); or
- treatment failure.

An adverse event is defined as "serious" (SAE) if it

- Results in death
- Is life threatening
- Requires or prolongs inpatient hospitalisation
- Results in persistent/significant disability/incapacity
- Is otherwise considered medically significant by the investigator.

Expected adverse events:

In this study the following events are potentially expected:

**ESWL:** bleeding on passing urine, pain, urinary tract infection, bruising of abdomen/loin skin, stone fragments stuck between kidney and bladder, infection, kidney damage and persistence of stones.

**Ureteroscopy:** burning or bleeding on passing urine, temporary insertion of bladder catheter, insertion of stent and further procedure to remove it, pain, inability to retrieve stone, movement of stone into kidney, kidney damage or infection, failure to pass the telescope, recurrence of stones, damage to ureter, scarring of ureter.

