## 4.2 Recording and reporting AEs and SAEs

### *Assessing and recording AEs and SAEs*

Non-serious events will not be collected or reported. Planned hospital visits for conditions other than those associated with the ureteric stone will not be collected or reported. Hospital visits (planned or unplanned) associated with further interventions to facilitate ureteric stone clearance will be recorded as an outcome measure, but will not be reported as serious adverse events.

Within TISU, 'relatedness' is defined as an event that occurs as a result of a procedure required by the protocol, whether or not this procedure is the specific intervention under investigation and whether or not it would have been administered outside the study as normal care.

Any SAEs related to the participants' ureteric stone treatment that are not further interventions to facilitate stone clearance (eg if a participant is admitted to hospital for treatment of infection) will be recorded on the serious adverse event form. In addition all deaths for any cause (related or otherwise) will be recorded on the serious adverse event form.

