## 5 OUTCOME MEASURES

### 5.1 Primary outcome measure

The study has a primary clinical and a primary economic outcome reflecting the multidimensional nature of the possible effects the intervention may have.

**Clinical** Clearance of ureteric stones operationally defined as "no further intervention required to facilitate stone clearance" up to 6 months from randomisation.

**Economic** Incremental cost per quality adjusted life years (QALYs) gained at 6 months from randomisation. QALYs are based on the responses to the EQ-5D.

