### 5.2 Secondary outcome measures

**Patient-reported** -measured at pre and 1 week post intervention, 8 weeks and 6 months post randomisation

Severity of pain as measured by the Numeric Rating scale (NRS), generic health profile as measured by the SF-12, (8 weeks and 6 months only), health status as measured by the EQ5D, use of analgesia, acceptability of received procedure (8 weeks and 6 months only)

**Clinical** Further interventions received, complications up to 6 months post randomisation

**Economic** NHS primary and secondary care use and costs up to 6 months, patient costs; incremental cost per surgical interventions averted.

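### Section 2 counts harms as a third primary outcome where Section 5 has only two, and Section 4.2 bars collection of non-serious events that the complications outcome would include

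*Protocol*

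**What the plan says.** **Status of harms.** Section 2 says that the clinical and cost-effectiveness of ESWL "will be determined with respect to the primary outcomes of" three numbered items: clearance, incremental cost per QALY, and "disease or treatment-related harms up to 6 months after randomisation". A second list follows, introduced by "These outcomes will be measured by". It has two bullets, one for the proportion needing no further intervention and one for cost-effectiveness. Neither concerns harms.

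Section 5.1 states: "The study has a primary clinical and a primary economic outcome". These are clearance and cost per QALY. The outcome paragraph of the Protocol Summary names the same two. Section 5.2 gives the secondary clinical outcomes as "Further interventions received, complications up to 6 months post randomisation".

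**Collection of harms.** Section 4.2 states: "Non-serious events will not be collected or reported". It then requires an SAE form for serious events related to stone treatment, other than further interventions for clearance, and for every death. Section 3.3.4 has sites enter complications on the 8-week and 6-month CRFs, and has participants answer questions on complications in their questionnaires at the same two times. Table 1 ticks complications at both times but gives the CRF as the only source. None of these places restricts complications to serious ones.

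**The concern.** A protocol should give one set of primary outcomes. A reader of Section 2 would expect a primary harms result, and a reader of Section 5 would not.

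The collection conflict has more practical weight. Section 2 justifies the non-inferiority design on the ground that ESWL is less invasive, so that patients and urologists would accept more failures, up to 20%. Complications are the other side of that trade. Section 1.2 cites a review in which they were less frequent after ESWL (RR 0.44, 95% CI 0.21 to 0.92). Several events that Section 4.1 expects, such as bruising, pain, and burning or bleeding on passing urine, would often fall short of that section's own criteria for a serious event. These are the events that a site would omit if it took 4.2 at its word.

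**Working it through.** The protocol gives no figure to reproduce here, so the check is a comparison of sections.

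**Step 1: count the primary outcomes.**

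| Place | Primary outcomes | Where harms sit |
|---|---|---|
| Section 2, numbered list | 3 | Third primary item |
| Section 2, list of measures | 2 measures | No measure |
| Protocol Summary | 2 | Not among the primary outcomes |
| Section 5.1 | 2 | Not among the primary outcomes |
| Section 5.2 | none | Complications, secondary |

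Section 2 stands alone with three, and its own list of measures covers only two of them. The non-inferiority margin and the power calculation in Section 7.1 concern clearance only. The weight of the document is therefore on two primary outcomes, with harms secondary.

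**Step 2: compare the collection rules.**

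| Place | Instruction | Limited to serious events? |
|---|---|---|
| Section 4.2 | Non-serious events neither collected nor reported | Yes, with no exception stated |
| Section 3.3.4 | Complications on site CRFs and in participant questionnaires, 8 weeks and 6 months | No |
| Section 5.2 | Complications to 6 months as a secondary outcome | No |
| Table 1 | Complications from the CRF, 8 weeks and 6 months | No |

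The 4.2 sentence covers collection as well as reporting, and it does not exempt the complications outcome. A non-serious complication therefore falls under two opposite instructions. The source also differs: CRF and questionnaire in 3.3.4, CRF alone in Table 1.

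**Step 3: what remains if a site follows 4.2 literally.** Treatment-related SAEs and all deaths are still recorded. Serious complications can still be entered on the CRF. Questionnaires go to participants from the study office (Section 6.3), so their reports of complications do not depend on how a site reads 4.2. What is lost is the site record of minor complications.

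**Step 4: the expected-event list.** Section 4.1 says that treatment failure is not an adverse event. Yet the expected events it lists for ESWL end with "infection, kidney damage and persistence of stones", and those for ureteroscopy include being unable to retrieve the stone. This is untidy beside the section's own exclusion. The list is headed as expected adverse events, and its evident use is the test in Section 4.2 of whether a serious related event is unexpected. Nothing makes it the list from which CRF complications are drawn.

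**The case against.** The best defence is that Section 4.2 concerns safety reporting only. Its heading is about adverse events, and the same paragraph separates the two streams: hospital visits for further intervention are recorded as an outcome but not reported as SAEs. On that reading a non-serious event gets no adverse event form, while complications stay on the CRF. This is probably what was meant, but the sentence does not say so, and its wording extends to collection.

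It is also fair that the conflict over primary status changes no analysis, since no margin, test or sample size attaches to harms. Definitions of complications and CRF completion rules may sit in documents not shown. Their absence is not the complaint; such guidance could clarify practice, but the protocol's own sections would still disagree. Because allocation is minimised by centre (Section 3.3.3), differences between sites in recording minor events would fall on both arms. The expected loss is in completeness and precision, with no direction of bias that can be shown.

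Two stronger readings are tempting.

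- A reader might infer that the harms objective cannot be answered at all. The documents do not support this. Complications over the same 6-month window are a secondary outcome with two sources in 3.3.4, and related SAEs and deaths are recorded besides.
- A reader might infer from Section 4.1 that clearance failures will be counted again as complications and distort the comparison. That would require the expected-event list to serve as the complications list, which the protocol does not say. Any size put on it would need complication rates by arm and a share of failures entered twice, and the protocol gives neither.

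**Conclusion.** The point holds as two contradictions in the text. First, Section 2 gives three primary outcomes, one of them without a measure, against two in the Protocol Summary and Section 5.1, with complications secondary in 5.2. Second, the unqualified rule in 4.2 conflicts with 3.3.4, 5.2 and Table 1 on whether non-serious complications are collected.

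The first is a matter of consistency and does not affect the power or the margin for clearance. The second could cost site-recorded minor complications, to an extent that depends on how many sites read 4.2 literally. The documents do not show this, so no numerical effect is claimed. Harms remain comparable from the CRFs, questionnaires, related SAEs and deaths. The conclusion assumes that complications were meant to include non-serious ones. The text does not restrict them, but neither does it say so outright.

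**What to change.** 1. **Section 2:** take item iii out of the primary outcomes and state it as a secondary harms objective, measured by complications up to 6 months, in line with 5.1 and 5.2.
2. **Section 4.2:** say that non-serious events are not reported as adverse events, but that complications of stone treatment, serious or not, are recorded on the 8-week and 6-month CRFs.
3. **Table 1:** give the source for complications as CRF and participant questionnaire, to agree with 3.3.4.
4. **Section 4.1:** leave the expected-event list as it is, because removing items could change which serious related events count as unexpected and go to the sponsor, ethics committee and DMC. Add a note that stone persistence or failed retrieval belongs to the clearance outcome and is not entered as a complication.

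The cost is protocol wording and a short note to sites on completing the CRF. No new form is needed, since complications are already on the CRF schedule. The downside is slightly more data entry at sites that had been leaving out minor complications.
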